### Secondary objectives

To assess the difference in % AF burden between groups at 12 months, with additional evaluations conducted and reported at the 6- and 15- month time points.The assess the total duration and frequency of AF episodes between groups at 12 months, with additional evaluations conducted and reported at the 6- and 15-month time points.To assess time to first AF recurrence following a DCCV or ablation (where ICM data is available prior to intervention)To assess the change in the following cardiac and metabolic parameters between groups at 12 months, with additional evaluations conducted and reported at the 6- and 15-month time points:

Weight, body mass index (BMI), waist circumferenceCardiorespiratory fitnessVisceral fatLeft atrial size and strain.Peri-atrial fat volume and atriomic signal.Systolic and diastolic blood pressureLow density lipoprotein, high density lipoprotein, total cholesterol, glycated HbA1c and C-reactive protein% of time active.

5. To assess the difference in the following patient-reported outcomes between groups at 12 months, with additional evaluations conducted and reported at the 6- and 15-month time points:

European Heart Rhythm Association (EHRA) scaleAtrial fibrillation effect on quality of life (AFEQT)EuroQol-5 dimensions-5 levels (EQ-5D-5L)Hospital Anxiety and Depression Scale (HADS)Holistic capability assessment using the ICEpop CAPability measure for Adults (ICECAP-A).NHS resource-use questionnaire.

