### Randomisation

Participants will then be randomised to either UC or SR using a web-based platform (Sealed Envelope: https://www.sealedenvelope.com/) in permuted blocks of four using an allocation sequence generated at random. Stratification will be by AF subtype (paroxysmal or persistent). Participants’ general practitioners will be informed of their patients’ involvement in the study and will be provided with a study information sheet.

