### Assessments

In addition to baseline measurements detailed above, the following assessments will be carried out at 6, 12 and 15 months (see figure 1).

Medication listAnthropometricsFasting blood tests.Seven-day photographic diet diary.Seven-day blood pressure diarySeven-day free living activity.AFSS questionnaire and EHRA classEQ-5D-5L, AFEQT, HADS, ICECAP-A and NHS resource use questionnaires.TTEDEXACPETA repeat CTCA with peri-atrial fat analysis will be carried out at 12 months only.

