### Data analysis

The distributional properties of the continuous variables will be examined by plots. Participant baseline characteristics and health outcomes will be summarised (including missing data) using descriptive measures: mean (SD) or median (IQR) for symmetric or skewed continuous variables, respectively; number (percent) for categorical variables; and mean (SD) absolute and percent change for longitudinal data will be reported separately by treatment allocation.

The primary outcome, change in AF symptom score, will be assessed using a two-way analysis of covariance (ANCOVA) adjusted for baseline score and AF type using data from subjects where both baseline and follow-up data are complete. The impact of missing follow-up data on the primary analysis will be explored with sensitivity analysis using methods such as last observation carried forward. This approach is likely to provide a conservative estimate of treatment effects. A prespecified secondary analysis will include a two-way ANCOVA for change in AF symptom score at 6 months, again adjusted for baseline score and AF subtype. To aid interpretation, changes will be considered in light of the minimally clinically important difference (MCID). While an anchor-based MCID has not yet been formally established for the AFSS, changes of approximately 3–5 points are considered clinically meaningful in analogous AF-specific instruments, such as the AFEQT. This range will be used to contextualise the clinical relevance of observed changes.

For continuous secondary outcomes, two independent samples t-tests or non-parametric alternatives will be used. Parametric assumptions will be checked by reviewing univariate histograms prior to formal analysis. For categorical secondary outcomes, change in status at follow-up will be compared between groups using χ² or Fisher’s exact test. Time to AF recurrence and event-free survival curves will be with Kaplan-Meier assessment and differences between curves tested with the log-rank test.

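### Continuous secondary outcomes are tested without adjustment for baseline or AF subtype, unlike the AF symptom score; the tests are valid but give up precision

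*Protocol article*

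**What the plan says.** All references are to the protocol article.

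- **Data analysis, AF symptom score.** The 12-month primary analysis is a "two-way analysis of covariance (ANCOVA) adjusted for baseline score and AF type". The 6-month analysis is a "two-way ANCOVA for change in AF symptom score at 6 months, again adjusted for baseline score and AF subtype".
- **Data analysis, other continuous outcomes.** "For continuous secondary outcomes, two independent samples t-tests or non-parametric alternatives will be used". Histograms of each variable decide between the two. The section names no covariate and does not say whether follow-up values or change scores are tested.
- **Secondary objectives.** The scale varies. For one group of outcomes the aim is "To assess the change in the following cardiac and metabolic parameters between groups at 12 months"; for AF burden it is "To assess the difference in % AF burden between groups at 12 months". The patient-reported outcomes are also worded as a difference.
- **Baseline assessments and Assessments.** Anthropometry, home blood pressure, activity, DEXA, echocardiography, exercise testing, AFEQT, EQ-5D-5L, HADS and ICECAP-A are all taken at baseline. "In addition to baseline measurements detailed above, the following assessments will be carried out at 6, 12 and 15 months". CT is repeated at 12 months only.
- **Randomisation.** Allocation is stratified by AF subtype, in permuted blocks of four. The implantable cardiac monitor (ICM) goes in after the baseline assessments and randomisation comes next. No monitoring period before randomisation is described.

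**The concern.** The plan accepts adjustment for baseline and for the stratification factor for one scale, then drops both for the other continuous outcomes without giving a reason. A t-test on follow-up values ignores what is known about each patient at entry. A t-test on change scores gives the baseline a fixed weight of one, which over-corrects when the correlation is modest. Neither uses the stratification factor.

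The quality-of-life, fitness and cardiac-structure conclusions will rest on these comparisons. With about 15 evaluable patients per arm, the arms can easily differ at baseline by chance, and wide intervals are the main threat to interpretation.

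**Working it through.** **1. The plan's own figure.** Sample size gives 30 evaluable patients from a one-tailed t-test, effect 0.93 SD, alpha 0.05, power 0.80. The normal approximation gives 2(1.645 + 0.842)² / 0.93² = 14.3, so 15 per arm. The t-test gives 15.02 per arm, with power 0.799 at 15. The figure reproduces, and 15 per arm is used below.

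**2. Inputs that are assumptions.** The article gives no r. The range 0.3 to 0.9 is assumed, with equal SDs at baseline and follow-up. Tests below are two-sided at 5%.

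**3. Variance of the treatment difference, relative to a follow-up t-test.**

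- Follow-up t-test: 1
- Change-score t-test: 2(1 − r)
- ANCOVA: 1 − r²

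The t-test SE divided by the ANCOVA SE is therefore 1/√(1 − r²) for follow-up values and √(2/(1 + r)) for change scores. The power columns take 15 per arm and a true difference of 0.93 SD of the follow-up value. That effect is borrowed from Sample size for illustration only. ANCOVA power includes a small-sample variance inflation of 1 + 1/25 and 26 degrees of freedom.

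| r | SE ratio, follow-up | SE ratio, change | Power, follow-up t | Power, change t | Power, ANCOVA |
|---|---|---|---|---|---|
| 0.3 | 1.05 | 1.24 | 0.69 | 0.55 | 0.71 |
| 0.5 | 1.15 | 1.15 | 0.69 | 0.69 | 0.79 |
| 0.7 | 1.40 | 1.08 | 0.69 | 0.89 | 0.92 |
| 0.9 | 2.29 | 1.03 | 0.69 | >0.99 | >0.99 |

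At a smaller assumed effect of 0.7 SD, simulated power (follow-up t / change t / ANCOVA) is 46/35/48% at r = 0.3, 46/46/56% at r = 0.5 and 47/65/71% at r = 0.7. The order is the same.

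**4. Check at the actual size.** A simulation of 6,000 trials per setting, with 30 patients and stratified blocks of four, gave mean SEs (follow-up t / change t / ANCOVA) of 0.362/0.428/0.352 at r = 0.3 and 0.362/0.162/0.161 at r = 0.9. The ratios are 1.03 and 1.22 at r = 0.3, and 2.25 and 1.01 at r = 0.9. The large-sample ratios therefore slightly overstate the gain at this size, but ANCOVA still has the smallest SE.

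**5. Validity.** With no stratum effect, simulated type I error was 0.047 to 0.054 for the two t-tests. With an assumed stratum effect of 0.5 SD, the follow-up t-test was mildly conservative (0.040 to 0.045, power about 0.66 to 0.67). The change-score test was unaffected (0.048 to 0.052), because a stable stratum difference cancels.

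**6. Chance imbalance.** Without adjustment, the difference in baseline means has SD √(2/15) = 0.365 baseline SDs. An imbalance of that size shifts a follow-up comparison by r × 0.365 and a change comparison by −(1 − r) × 0.365. At r = 0.7 these are 0.26 and −0.11 SD; at r = 0.3 they are 0.11 and −0.26 SD. ANCOVA removes this shift in expectation.

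**7. ICM outcomes.** AF burden, episode duration and episode frequency have no described pre-randomisation value, so only AF subtype can be adjusted for. With two equal strata differing by 0.5 SD (assumed), the unadjusted variance is 1 + 0.5²/4 = 1.0625 and the SE ratio is √1.0625 = 1.03.

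**The case against.** The strongest reply is that nothing is broken. Randomisation makes the t-test unbiased, its type I error is near nominal, and the article claims no power for secondary outcomes. Secondary objectives words the cardiac and metabolic outcomes as change. If change is what is tested, highly correlated measures lose little: an SE about 8% larger at r = 0.7 and 3% at r = 0.9. Non-parametric alternatives already offer something for skewed data. All of this stands, and it limits the point to efficiency and to robustness against chance imbalance.

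It does not dispose of the point. The scale is not fixed in Data analysis, and neither t-test scale does well across the range: follow-up values lose most at high r, change scores at low r. The patient-reported outcomes, worded as a difference at 12 months, are the more exposed group. A separate analysis plan may refine the method, but the article states a method rather than leaving it open.

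Four stronger readings are tempting and are not supported:

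- **That the section contradicts itself.** It assigns different methods to different outcomes and nowhere promises adjustment for the secondary ones. This is an inconsistency of approach.
- **That the unadjusted results would be biased.** They are off only conditional on a chance imbalance.
- **That every continuous secondary outcome has a baseline.** The ICM outcomes do not, as far as the article describes.
- **That EHRA class needs an adjusted ordinal model.** The categorical rule says "change in status at follow-up will be compared between groups using χ² or Fisher’s exact test". With about 30 patients an exact test is defensible, and proportional-odds regression would be a debatable preference.

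**Conclusion.** The point holds as a recommendation on efficiency, of minor to moderate weight and confined to secondary outcomes. The unadjusted tests are valid but less precise than the model already chosen for the AF symptom score. Over the assumed range of r from 0.3 to 0.9, the large-sample SE penalty rises from about 5% to 129% if follow-up values are tested and falls from about 24% to 3% if change scores are tested. At 30 patients the penalties are slightly smaller.

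The direction is secure for outcomes with a baseline; the size is not, because it rests on r and on the untold scale. For the ICM outcomes the gain comes from AF subtype alone: about 3% in SE under the assumed 0.5 SD stratum difference.

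**What to change.** Amend Data analysis as follows:

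- For each continuous secondary outcome with a baseline value, fit ANCOVA on treatment, baseline value and AF subtype. With baseline in the model, the treatment estimate is the same whether follow-up or change is the response, so the open choice of scale no longer matters.
- For AF burden and for episode duration and frequency from the ICM, adjust for AF subtype alone.
- Report adjusted differences with 95% confidence intervals.
- Judge assumptions on model residuals rather than on histograms of single variables. For skewed measures use a transformation or rank-based ANCOVA.

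The cost is wording and up to two degrees of freedom per model. No patients, visits or measurements are added. According to Study status, recruitment was complete and follow-up still running at submission, so the change should be dated and documented before unblinded outcome analysis. If that analysis has already taken place, label the adjusted results as added afterwards.

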### Sample size

We aim to recruit 36 patients. The sample size was estimated using a one-tailed two independent sample t-test with a standardised effect size of 0.93 (estimated using a previous publication in a similar population using the same assessment methodology)^40^ with an alpha of .05 and power of .80 producing a sample size of 30 to detect a difference in AF symptom score. A 20% drop-out rate has been factored in to give a total sample size of 36 randomised 1:1.

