### Inclusion criteria

Symptomatic paroxysmal or persistent AF.Aged ≥18 years.Patient has been referred for AF CA and/or DCCV as a result of routine clinical care.BMI ≥27 kg/m^2^

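### If EHRA class falls under the χ²/Fisher rule for categorical outcomes, as is most natural, the test discards the ordering of the scale and loses power

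*Protocol article*

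**What the plan says.** The Data analysis section of the protocol article sets two rules for secondary outcomes, apart from time-to-event outcomes.

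- Categorical: "For categorical secondary outcomes, change in status at follow-up will be compared between groups using χ² or Fisher’s exact test".
- Continuous: "For continuous secondary outcomes, two independent samples t-tests or non-parametric alternatives will be used".

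Rank methods are therefore offered only on the continuous side. The article does not define status or its categories, and it does not sort the listed outcomes into the two groups.

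Secondary objectives lists the EHRA scale among the patient-reported outcomes to be compared between groups at 12 months, and also at 6 and 15 months. Baseline assessments places it with the AFSS under AF symptom burden. Assessments calls it a class. The other listed outcomes in Secondary objectives are questionnaire instruments or measured quantities.

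**The concern.** A symptom class is ordered. Applied to three or more change categories, χ² and Fisher's exact test treat better, unchanged and worse as interchangeable labels. Collapsed to improved or not, they lose the size of the shift. Either way the test does not use all that the scale says about whether Super Rehab patients end up less symptomatic.

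Entry requires "Symptomatic paroxysmal or persistent AF" and referral for ablation or cardioversion, so patients in both arms may improve through routine rhythm treatment. How far and in which direction each arm moves is then the informative part.

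At stake is the second symptom measure, the natural support for the primary AFSS result. With 15 to 18 patients per arm there is little power to spare.

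**Working it through.** **1. The plan's own figure.** Inputs from Sample size: "one-tailed two independent sample t-test with a standardised effect size of 0.93", "with an alpha of .05 and power of .80 producing a sample size of 30 to detect a difference in AF symptom score". With the normal formula, n per arm = 2(z₀.₉₅ + z₀.₈₀)²/d² = 2(1.645 + 0.842)²/0.93² = 14.3, rounded up to 15, so 30 in total. The exact one-sided t-test needs 15.02 per arm and has power 0.799 at 15. The stated 30 reproduces. With "A 20% drop-out rate has been factored in to give a total sample size of 36 randomised 1:1", 30 × 1.2 = 36, or 18 per arm. I use 15 and 18 per arm below. The article gives no figure for EHRA.

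**2. Assumptions for EHRA.** The article gives no class distribution, so the control-arm distributions below are assumed. The Super Rehab arm is shifted by 0.93 SD on a latent normal scale: cumulative probability = Φ(Φ⁻¹(control cumulative probability) + 0.93). For example, 25% improved in controls becomes Φ(−0.674 + 0.93) = Φ(0.256) = 60%. Tests are two-sided at 5%, with 1,500 simulated trials per row and a Monte Carlo error of about 1 to 1.5 points.

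| Assumed control distribution | n per arm | χ² | Fisher | Rank test | Loss (points) |
|---|---|---|---|---|---|
| 5 levels, 10/25/30/25/10% | 15 | 35% | 39% | 63% | 24–28 |
| same | 18 | 44% | 46% | 72% | 26–28 |
| 4 levels, 15/40/35/10% | 15 | 41% | 42% | 61% | 19–20 |
| same | 18 | 48% | 50% | 68% | 18–20 |
| improved/same/worse, 25/55/20% | 15 | 45% | 41% | 57% | 12–16 |
| same | 18 | 53% | 52% | 64% | 11–12 |

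**3. Change coded as improved or not.** Take a four-level change (two classes better, one better, same, worse) cut at −1.2, −0.2 and 1.2 SD, with the same shift.

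- On all four levels, χ² has 42% power against 61% for the rank test at 15 per arm, and 50% against 70% at 18.
- Collapsed to improved or not, Fisher has 33% and 48%, and χ² has 50% and 62%.
- Losses against the rank test at 15 per arm are 61 − 33 = 28 (Fisher) and 61 − 50 = 11 (χ²). At 18 they are 70 − 48 = 22 and 70 − 62 = 8.

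The low end is soft. Collapsing the 25/55/20% distribution instead and using uncorrected χ², a check with 4,000 trials put the loss at only about 6 points (15 per arm) and 2 points (18 per arm).

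**4. Null behaviour.** With no difference between arms, all three tests rejected in about 3–6% of trials.

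**5. Illustrative tables (improved/same/worse).**

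- A directional shift, 11/6/1 against 5/10/3. The expected counts are 8, 8 and 2 in each arm, so χ² = 2(9/8 + 4/8 + 1/2) = 4.25 on 2 df and p = 0.12. Fisher p = 0.21; rank p = 0.045.
- More improvers and more worseners in one arm, 6/6/3 against 1/13/1. The expected counts are 3.5, 9.5 and 2, so χ² = 2(6.25/3.5 + 12.25/9.5 + 1/2) = 7.15 on 2 df and p = 0.028. Rank p = 0.32.
- A pure difference in spread, 10/80/10% against 40/20/40%. χ² and Fisher reject in 88–93% of trials, the rank test in about 8%.

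**The case against.** The article never assigns EHRA to the categorical rule. It uses both scale and class for it. If EHRA were scored as a number, the non-parametric route would already be open. That stands: the categorical reading is the likelier one, but it is an inference.

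A reader might infer that the planned test always ignores direction and can declare a difference without benefit. The article does not support this, because it does not say how change is coded. An improved/not-improved comparison has a direction, and a significant result then means a higher improvement rate in one arm. The problem arises only with three or more change categories. Even there, the planned descriptive summary by arm ("number (percent) for categorical variables") would expose a pattern of more improvers and more worseners.

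A reader might also infer that the starting class is ignored. It is not: change is measured from it. What is absent is covariate adjustment for it.

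The power figures rest on chosen distributions and on an effect size that belongs to the AFSS score, not to a coarser class. The rank test itself misses about 28–43% of true shifts here, so much of the low power comes from the sample size. This limits the size of the point but does not remove it: the order-respecting test was ahead under every coding examined.

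**Conclusion.** The point holds in a conditional form. If EHRA class is analysed under the categorical rule, as is most natural, the stated test discards ordering that a rank or ordinal method would use. In the settings worked through, power is about 33–62% with χ² or Fisher against about 57–72% with a rank test, a like-for-like loss of about 8–28 percentage points. The loss is largest with many levels, or with Fisher on a binary coding. It can fall to a few points with uncorrected χ² on a binary coding. These figures assume the distributions shown, a borrowed 0.93 SD shift and two-sided 5% tests.

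This is not a validity failure. χ² and Fisher keep their type I error, and the primary ANCOVA on the AFSS is untouched. The matter is a minor one: a cheap gain in efficiency and clarity on one secondary outcome.

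**What to change.** State which rule covers EHRA. For EHRA, replace χ²/Fisher with an ordinal comparison of 12-month class: a proportional-odds model on arm, adjusted for baseline class and AF subtype. If cells are too sparse for that model, use a rank test on change in class stratified by AF subtype. Keep χ² or Fisher for binary and nominal outcomes.

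The cost is one sentence and no new data. The downside is the proportional-odds assumption and possible instability with about 30 patients, both of which the rank test avoids. Study status reports follow-up as still ongoing at submission, so the choice should be fixed before outcomes by arm are seen by those doing the analysis.

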### Study governance

The trial management group (TMG) will monitor progress. Any adverse events will be reported to the trial steering committee (TSC). The TSC will be consulted for advice as required and monitor study progress. They will meet at baseline and 12 months with any additional meetings organised on request by the TMG. The data monitoring committee will meet at study initiation and then meet to review unblinded data at 12- and 24-month time points, alongside any additional safety issues for the trial and relevant information from other sources and advise the TSC on whether there are any ethical or safety reasons why the trial should not continue. They will also determine whether any additional interim analysis of trial data should be undertaken.

### Patient and public involvement

The NHS Research and Development office for Bath, Swindon and Wiltshire has supported our patient and public involvement (PPI). We collected PPI feedback through BSW’s dedicated group ‘PARTCIPATE’ and consulted with another patient PPI group within the *Cardiologist’s Kitchen* and *CardioFITr* programmes (run by clinicians in Bath). Patient-facing material was amended based on their feedback and we also integrated sample dietetics/exercise sessions for those in UC at the end of the study if requested by the participant. The primary outcome of symptom burden was selected by the clinical team, as it is often the key driver in decision-making around rhythm-control strategy management, including escalation to invasive treatments.

## ethics and dissemination

Ethics approval was granted by London-Chelsea Research Ethics Committee (reference: 22/LO/0479, 22/08/2022) and participants will provide written informed 21 consent prior to any study-related activities. Study findings will be discussed with participants and other relevant stakeholders (commissioners, charities, clinicians and members of the public). Results will be presented at national and international conferences as well as submitted for publication in a peer-reviewed journal.
